**Selection of Study Population**

**Recruitment**

All patients with incomplete SCI will be screened at admission to inpatient rehabilitation for initial eligibility. Typical inpatient rehabilitation length of stay at BSWIR varies based on factors including what is deemed medically appropriate by the SCI Medical Director ([name], Co-Investigator), approval by the insurance company, medical complexity, and rate of recovery. However, the average length of stay over the past year at BSW was 35 days for traumatic SCI and 22 days for non-traumatic SCI. Usual care rehabilitation is initiated within 24 hours of admission. Standard research recruitment procedures for our program may include family education materials and research flyers, as well as research coordinators educating clinicians and patients/families. [name] will support recruitment through team conference and patient rounding.

**Subject Information and Screening** - We will screen all patients with SCI upon admission for initial eligibility (see **Table 2** and **3** for inclusion & exclusion criteria). Screening and patient suitability will be discussed at the twice weekly SCI clinical team rounding meeting. Study staff will approach identified individuals who meet the inclusion/exclusion criteria during the first 7 days in a private setting and briefly explain the study and answer any patient questions for clarification. The patient will be given adequate time to determine if they want to participate in the study.

**Study Period**

Patients will participate for the duration of their length of stay for inpatient rehabilitation, from the time they consent after admission to the time they discharge.

**Rationale for Selection of Dose**

Our proposed project is also rooted in principles of neuroplasticity ^(47, 48)^ (**Table 2**) and exercise prescription dose^(88)^ (**Table 3**). The 10 principles of neuroplasticity and 4 principles of exercise prescription dose – **especially specificity, intensity, and timing** – are driving forces to initiate RGT during inpatient rehabilitation. With clear resonance between neuroplasticity and exercise dose principles, this project will describe and relate RGT dose parameters with gait and functional outcomes.

| **Table 2: Link between Principles of Neuroplasticity and specific aims** | | |
| --- | --- | --- |
| **Principle** | **How Principle is Addressed in the Robotic Gait Training (RGT) Program** | **Specific Aim** |
| *Use it or lose it* | Initiation of RGT as integrated into a comprehensive rehabilitation program when patients meet inclusion criteria. Intent to stimulate specific brain and spinal cord functions with task specific activities as soon as possible to prevent CNS pathway degradation. | AIM 2 |
| *Use it and improve it* | RGT facilitates the patient for task specific gait activity over the extended time of the inpatient rehabilitation stay. | AIM 2 |
| *Specificity* | RGT specifically address the individual patient’s mobility and movement patterns to aid reach the patient reach his/her goals. | AIM 2 |
| *Repetition matters* | RGT activities are completed in addition to skilled therapy intervention while in the inpatient rehabilitation setting. The patient repeats the RGT over several sessions, therefore developing greater patterns for recovery during inpatient rehabilitation stay and upon discharge. | AIMS  2 & 3 |
| *Intensity matters* | RGT is implemented based upon individual patient activity tolerance. RGT intensity (e.g., heart rate, # of steps, up time, walk time) is assessed daily and modified by therapist. Patients are verbally encouraged to continue increasing intensity as tolerated by staff. | AIMS  2 & 3 |
| *Time matters* | The program is initiated for appropriate patients during inpatient rehabilitation when the potential for neuroplasticity is greatest.^60^ | AIMS  2 & 3 |
| *Salience matters* | RGT is a gait task specific activity and integrates into the patient’s function and goals. Patients are encouraged by continued awareness of successful activity either by therapist, family, or another patient involved in program. | AIMS  1 & 2 |
| *Age matters* | Patients begin station activities as soon they meet inclusion criteria and activities are specifically selected for the individual patient’s need. |  |
| *Transference* | Based on clinical practice guidelines, robotic exoskeleton literature, and our prior work, the physical therapist facilitates the RGT program activities for the patient that are strategically chosen to allow for integration and progression from robotic gait training to overground gait training. | AIMS  2 & 3 |
| *Interference* | The RGT program focuses on specific motor recruitment, movement patterns, and maintenance of range of motion to decrease maladaptive plasticity and disruptions of learning. | AIM 2 |

| **Table 3. Link between Principles of Exercise Prescription and specific aims** | | |
| --- | --- | --- |
| **Principle** | **How Principle is Address in the Robotic Gait Training (RGT) Program** | **Specific Aim** |
| *Frequency (F)* | The anticipated frequency of the RGT sessions will be 3x/week. This is based on American College of Sports Medicine cardiorespiratory guidelines for people with SCI^88^ and preliminary results from our Feasibility and Retrospective studies. | AIMS  2 & 3 |
| *Intensity (I)* | We will monitor and assess intensity of RGT sessions using the following methods:^88,89^ heart rate (percent of maximal HR), Ratings of perceived exertion (RPE),^90^ and step count.^42,91^ For cardiometabolic health benefits, people with SCI are recommended to engage in moderate to vigorous intensity of aerobic exercise.^88^ As a rule of thumb, a person doing moderate-intensity aerobic exercise can talk, but not sing, during the activity. A person doing vigorous-intensity exercise cannot say more than a few words without pausing for a breath. | AIMS  2 & 3 |
| *Time (T)* | The anticipated duration of the RGT sessions based on preliminary results from our Feasibility and Retrospective studies will be up to 45 min/session. | AIMS  2 & 3 |
| *Type (T)* | The mode of exercise will be walking in the Ekso during RGT. Interventions that are intended to improve walking function are most effective when they incorporate task-specific gait training to directly engaging the neural circuits required for.^36^ | AIMS  2 & 3 |

**Eligibility Criteria**

Individuals (n = 128) between the ages of 16 – 85 years within 6 months post-incomplete SCI who are admitted to BSW and who meet criteria to use an EKSO robotic exoskeleton will be recruited to participate in this study. Subjects must meet Ekso robotic exoskeleton frame limitations unless per the discretion of the PI it is determined that subject’s weight and/or height being outside of this range does not interfere with the fit of the device. Patients will be screened at admission for initial eligibility and qualifying patients will be approached to participate. Patients will be evaluated by clinicians to determine if they meet the inclusion/exclusion criteria during their inpatient stay. If a patient is not initially appropriate for intervention due to medical reasons and later determined to appropriate during their stay, they may be approached to consent to participate. In a private setting, patients, and their caregivers if applicable, will be approached about the study and a study team member will briefly explain the study and answer any patient questions for clarification. Caregivers of minors will sign consent form and minors will be given an opportunity to assent to project. Inclusion/exclusion listed below.

| **Table 4. Eligibility Criteria** | |
| --- | --- |
| **Inclusion Criteria** | **Rationale** |
| 16-85 years of age | Broad range for generalizability; Our inpatient rehabilitation facility admits patients with SCI who are 16 years and older. Patients who are 16 and 17 years of age are likely to receive similar gait interventions as adults aged 18+ and able to meet manufacturer height and weight specifications of the Ekso robotic exoskeleton device. This is consistent with previously published exoskeleton research.^1^ 97% of patients at BSW were between 18-70 with average age of SCI admissions over the past 5 years being 56.0 ± 18.6 years. |
| All types of incomplete SCI (traumatic and non-traumatic) | Broad range for generalizability. In this study, we will include people with incomplete SCI regardless of presence of tetraplegia or paraplegia (~68% of all people with SCI)^15^ because of the greater potential for motor recovery. |
| Acute/Subacute phase of recovery | We will include patients with incomplete SCI admitted to BSW for inpatient rehabilitation within 6 months post-SCI (~88% of admissions over the past 5 years). |
| Medically stable as deemed by physician | Cardiac risk factors will be considered by the Medical Director of the SCI Team as well as additional co-morbidities |
| Undergoing medical care and rehabilitation at BSW | Patients with SCI will be accessible for recruitment. 1,128 patients with SCI were admitted for rehabilitation at BSW over the past 5 years. |
| Both genders and all races and ethnicities | Achieve a representative sample based on the population admitted at BSW (64% white, 36% minority past 3 years) and national statistics (78% of new cases of SCI are male).^15^ |
| Meet the Ekso robotic exoskeleton frame limitations | Frame limitations include: weigh 220 pounds (100 kilograms) or less; between 5’0” and 6’4” tall; have a standing hip width of 18” or less; have near normal range of motion in hips, knees, and ankles; able to attain a neutral ankle dorsiflexion with < 12 degrees of knee flexion); no more than 12 degree hip flexion contracture; no upper leg length discrepancy greater than half an inch (> .5”) or lower leg discrepancy greater than three-quarters of an inch (>.75”). |
| Continence of or a program for bladder and bowel management | Incontinence may contaminate the robotic exoskeleton and prevent its continued use in the study. While the soft padding may be able to be cleaned, it is possible that body fluids associated with incontinence may ruin the mechanical joints and actuators. All of our patients with SCI are either continent or on a bladder and bowel program. |

**Exclusion Criteria**

| **Table 5: Exclusion Criteria** | |
| --- | --- |
| **Exclusion Criteria** | **Rationale** |
| Moderate to severe TBI | Issues with central executive functions which can affect an individual’s memory for new information, planning, task switching, and action monitoring. |
| Degenerative diagnoses | Functional improvements are dependent on the nature of the non-traumatic etiology, as some are degenerative and may even be terminal, in the case of neoplasms or amyotrophic lateral sclerosis.^19^ |
| Wound located in proximity to the exoskeleton frame | Skin integrity issues that interfere with wearing the exoskeleton may worsen an existing wound with use during RGT. Screening for skin integrity issues is standard screening protocol for Ekso. |
| Severe osteoporosis/-penia as shown with DXA | In a recent systematic review, the incidence of bone fracture at any time during RGT is 3.4% (95% CI: 0.7%–8.1%).^95^ Generally accepted criteria for safe use include ability to stand using an assistive device and absence osteoporosis and existing fractures.^95^ |
| Pre-morbid developmental disability, significant psychological diagnosis, or other cognitive impairment | Identify individuals unable to independently understand instructions – assessed by the Orientation Log (O-LOG), a cognitive assessment tool, to identify the ability for normal orientation.^96^ This tool will be used to exclude cognitively impaired subjects. If the patient does not receive a score of 25 out of 30 or greater, then the patient will not be cleared to consent. |

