**Visit Windows**

Patients will be asked to complete testing at 2 time points: within one week of admission to inpatient rehabilitation and within one week of discharge from inpatient rehabilitation.

| **Table 6: Patient Timeline** | | | | |
| --- | --- | --- | --- | --- |
| Study Phase | Admission | Treatment (UC or RGT) Intervention | Discharge | Data Source |
| **Consent** | X |  |  |  |
| Demographics | X |  | X | Medical Record |
| **Outcome Testing** |  |  |  |  |
| *Aim 2* |  |  |  |  |
| Walking Score Index for Spinal Cord Injury (WISCI-II) | X |  | X | Medical Record |
| 10-meter walk test (10MWT) | X |  | X | Medical Record |
| Spinal Cord Independence Measure (SCIM) | X |  | X | Medical Record |
| Numeric Pain Rating Scale (NPRS) | X |  | X | Medical Record |
| Fatigue Severity Scale (FSS) | X |  | X | Study Specific |
| Penn Spasm Frequency Scale (PSFS) | X |  | X | Study Specific |
| Patient Health Questionnaire – 9 (PHQ-9) | X |  | X | Study Specific |
| General Anxiety Disorder – 7 (GAD – 7)  International SCI Quality of Life Basic Data Set  Qualitative Questionnaire | X  X |  | X  X  X | Study Specific  Study Specific  Study Specific |
| *Aim 3* |  |  |  |  |
| Heart Rate (HR) |  | X |  | Study Specific |
| Ratings of Perceived Exertion (RPE) |  | X |  | Study Specific |
| Number of steps |  | X |  | Study Specific |

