**Screening**

During the screening for consent process, the study staff will utilize the Orientation log (O-LOG), a cognitive assessment tool, to identify the ability for normal orientation. If the patient receives a score of >25 out of 30, the patient will be deemed to have normal orientation necessary for independent consenting and will be cleared to consent.

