**Risks and Benefits**

*Physical risks***:** Participants may experience orthostatic hypotension, skin breakdown, falls, fracture, overheating, and autonomic dysreflexia if they have difficulty due to impaired motor and sensory function common to SCI population. All therapy staff is trained to observe and monitor for these risks and methods to limit or resolve these potential concerns.

*Psychological risks***:** Participants may experience frustration during RGT due to motor and sensory deficits common to SCI population. All staff is trained to observe and monitor for frustration and methods to limit or resolve these potential concerns (i.e. institute rest breaks, maintain supervision).

*Social risks***:** No social risks have been identified by participating in this study.

*Legal risks***:** No legal risks have been identified by participating in this study.

*Economic risks*: No economic risks have been identified by participating in this study.

*Direct benefit to research participants*

See below for potential future benefits.

*Potential future benefits to individuals with the condition being studied*

The benefits to participants may include gaining greater walking function and improved health. Study findings could help rehabilitation clinicians identify evidence-based practice walking interventions and facilitate best practice guidelines for patients with SCI.

*Potential benefits to society in general*

The information gained in this study will help validate the importance and benefits of exoskeleton gait training in the outpatient rehabilitation setting for spinal cord injury patients.

*Potential benefits to others involved in research*

Clinicians involved in this research will contribute to evidence-based practice research methods, and facilitation of improvements for best practice for spinal cord injury patients.

*Risk to benefit analysis*

The risks posed to study subjects (e.g. injury while engaging in physical activity, psychological stress associated with treatment) are minimal, while the study poses benefits to the study participants in terms of improved walking recovery after SCI and overall health and function. The research poses potentially great benefits to society, as individuals with SCI and rehabilitation clinicians desire enhanced walking recovery to allow greater independence with mobility for activities and community participation.

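### The bone-health exclusion in Table 5 is narrower than the safe-use criteria in its own rationale, omits existing fracture, and depends on a DXA for which the protocol gives no source

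*Protocol*

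**What the plan says.** The bone-health row of Table 5 (protocol section 4, Exclusion Criteria) reads "Severe osteoporosis/-penia as shown with DXA". Its rationale column cites a systematic review for a fracture incidence during RGT of 3.4% (95% CI 0.7% to 8.1%) and continues: "Generally accepted criteria for safe use include ability to stand using an assistive device and absence osteoporosis and existing fractures".

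On how eligibility is established, section 4 (Eligibility Criteria) says: "Patients will be evaluated by clinicians to determine if they meet the inclusion/exclusion criteria during their inpatient stay". The Screening paragraph in section 5 describes one instrument: "the study staff will utilize the Orientation log (O-LOG), a cognitive assessment tool, to identify the ability for normal orientation". The physician's medical-stability criterion in Table 4 carries the rationale "Cardiac risk factors will be considered by the Medical Director of the SCI Team as well as additional co-morbidities".

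Section 4 (Study Treatment, RGT) adds a condition for starting the device: the patient must tolerate 15 minutes of standing without orthostatic intolerance. Section 12 (Risks and Benefits) lists fracture among the physical risks: "Participants may experience orthostatic hypotension, skin breakdown, falls, fracture, overheating, and autonomic dysreflexia".

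**The concern.** The row exists to limit fracture risk in the exoskeleton, and its rationale sets out three conditions for that purpose. The criterion beside it takes up only part of one. A reader applying Tables 4 and 5 as written would have no stated ground to exclude a patient with osteoporosis that is not severe, a patient with osteoporosis but no DXA, or a patient with an existing fracture.

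Traumatic injuries are eligible and the age range runs to 85, so such patients are foreseeable. At stake is whether the written rule lets people be randomised to RGT who fall outside the safe-use criteria that the protocol itself cites, and whether two clinicians screening the same patient would reach the same answer.

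**Working it through.** The protocol states no figure on this point that could be reproduced. The check is a comparison of texts.

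**1. The three cited conditions against the entry criteria (Tables 4 and 5).**

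| Condition in the Table 5 rationale | Entry criterion | Elsewhere in the protocol |
| --- | --- | --- |
| Able to stand with an assistive device | None | Partly covered: 15-minute standing tolerance before RGT starts (section 4, RGT) |
| No osteoporosis (no severity qualifier) | Excluded only if severe and shown by DXA | Not addressed |
| No existing fracture | None | Not addressed as a condition; fracture appears only as a risk (section 12) |

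The fracture row is the clearest gap and needs no inference. In the osteoporosis row the criterion adds two restrictions that the rationale does not contain. The suffix for osteopenia blurs it further: if severe osteopenia excludes, a reader may suppose that all osteoporosis does too, yet the text does not say so.

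**2. Where the DXA would come from.** DXA is named once in the protocol, in this row. It is absent from the recruitment and consent text, from the Screening paragraph, from Table 6 and from the data lists in sections 6 and 13. Other items do have a stated basis: the O-LOG has a cut-off, skin checks are described as standard screening for the device, and the AIS grade is taken from the medical record as standard care. For DXA there is no source, no skeletal site and no cut-off for severe. Because the exclusion applies only when DXA shows the condition, a patient with no DXA cannot meet it as worded.

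**3. Whether another rule closes the gap.**
- Medical stability is a physician's judgement. Its rationale names cardiac risk and co-morbidities, not bone or fracture.
- Eligibility Criteria also requires that patients qualify for the Ekso device. The requirements spelled out are frame limits: weight, height, hip width, joint range, contracture and leg length.
- The standing condition applies only in the RGT arm. It governs the start of training rather than entry (randomisation follows consent), and it tests orthostatic tolerance.

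Each may catch some patients. None requires a check of bone density or fracture.

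**4. Scale of the background risk only.** Inputs are the cited incidence p and 64 patients per arm (section 9). The assumption is that the cited rate applies per patient to this RGT arm. Expected fractures are 64 × p, and the chance of at least one is 1 − (1 − p)^64.
- p = 0.034: 64 × 0.034 = 2.2; 1 − 0.966^64 = 0.89
- p = 0.007: 64 × 0.007 = 0.4; 1 − 0.993^64 = 0.36
- p = 0.081: 64 × 0.081 = 5.2; 1 − 0.919^64 = 0.996

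These figures describe total risk at the cited rate. They do not measure what the narrow wording adds.

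**The case against.** The strongest reply is that this is a single institution with its own SCI physicians. Clinicians evaluate every patient against the criteria, suitability is discussed at team rounds, and the Medical Director considers co-morbidities. Such a team would be unlikely to put a patient with a known unstable limb fracture into the device. That is fair as a prediction of practice, and it lowers the likely number affected. It does not supply a written rule.

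Several stronger readings are tempting, and the protocol does not support them:
- **That the trial never obtains a DXA.** Table 6 lists no eligibility checks at all, not even the O-LOG or the frame measurements, so absence there proves little. A scan may already be in the medical record. What can be said is that the protocol does not schedule one or say where it comes from.
- **That the protocol calls these patients unsafe.** The row reports criteria that it describes as generally accepted. It does not adopt them as its own or label anyone unsafe.
- **That standing ability is ignored.** The condition for starting RGT covers it in part.
- **That the row will exclude almost nobody.** The availability of DXA is not given, so this cannot be known.
- **That 2.2 fractures, or the 89% chance of at least one, is the cost of the wording.** Those are totals at the cited rate, not an excess.
- **That fractures would distort the safety comparison.** Fractures during RGT are what a comparison between arms should detect, and the DSMB reviews events by arm each quarter.

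How strict a bone threshold should be is a clinical choice and is not disputed here.

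**Conclusion.** The point holds in a limited form. Within one table row, the exclusion and its rationale disagree on severity and on existing fracture. The exclusion also depends on a test result whose source the protocol does not state. As written, patients who do not meet the cited safe-use criteria can be randomised to RGT, and section 12 names fracture as a risk.

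The size cannot be given. The protocol does not report the share of entrants with osteoporosis or an existing fracture, the share with a DXA, or how fracture risk differs between those inside and outside the cited criteria. The conclusion assumes only that Tables 4 and 5 are applied as written; clinical judgement may narrow the gap in practice. Because it bears on patient safety and costs little to correct, the sponsor should act on it.

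**What to change.** Amend the Table 5 row and the screening text so that they agree:
- Reconcile the criterion with its rationale, either by aligning the two or by stating which of the cited conditions are not applied and why. Clarify what the osteopenia suffix covers.
- Address existing fracture explicitly and say which fractures are meant. Traumatic SCI is included, and an unqualified reading could exclude patients for a spinal fracture that is part of the injury.
- State what information decides the criterion and how a patient without a DXA is classified.
- Apply the same rule before randomisation in both arms.

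The clinical threshold, the evidence that suffices and whether DXA is needed are for the sponsor to decide.

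The cost is a protocol amendment and a line on the screening form. Some more patients may be screened out; the protocol gives no basis for estimating how many.
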